### Statistics

Given the unknown 1 year LTP rate for intermediate-size CRLM for both techniques, it was not possible to apply validated assumptions for both proportions. Hence a difference in 1y-LTP rate of more than one third (33%) is considered clinically relevant as it seems unlikely that a smaller difference will significantly impact overall survival. Most 1-year LTP will either be re-ablated or patients will receive systemic chemotherapy because of the simultaneous presence of extensive distant progression. In other words, unablatable LTP at 1-year without recurrence at distant sites is uncommon. We therefore accept that a difference in 1 year LTPFS of more than one third (0.33) will reject the null hypothesis concluding that the techniques are significantly different [17]. Group sample sizes of 33 in group 1 and 33 in group 2 achieve 81.059% power to detect a difference between the group proportions of −0.33. The proportion in group 1 (the treatment group) is assumed to be 0.665 under the null hypothesis and 0.3350 under the alternative hypothesis. The proportion in group 2 (the alternative treatment group) is 0.665. The test statistic used is the two-sided Z-test with un-pooled variance. The significance level of the test is 0.05. To account for a 3% loss to follow-up (= 2 patients) we need to randomize 34 patients (NR) into each of the two arms.

Baseline patient-, tumour- and treatment characteristics will be described and compared between the two treatment arms using the Chi-square test for categorical variables and the independent two-sample t-test, ANOVA or Mann–Whitney-U-test for continuous variables. *P* values below 0.05 will be considered significant. When appropriate, box-plots and cross-tables will be used for descriptive statistics of continuous and categorical variables, respectively. One year LTPFS rates will be compared between MWA and SBRT using the Chi square test. To determine hazard ratios (HR) for multivariate analysis, logistic regression will be used. Univariate LTPFS time analysis will be performed using the Kaplan–Meier method with corresponding two sided 95% confidence intervals (CI). Differences in LTPFS length will be analysed using the log rank test.

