### Study Cohort

Patients eligible for percutaneous ablation will be randomized prior to the procedure into one of two study arms: percutaneous MWA (arm A) or SBRT (arm B). Patients with at least one additional CRLM requiring resection will undergo laparoscopy or laparotomy with surgical inspection of the abdominal cavity and intraoperative ultrasound (IOUS) and if still considered eligible randomized intraoperatively. If randomized to MWA during open laparotomy, the eligible tumours will be ablated in the same procedure using ultrasound guidance. Patients included in study arm B will undergo SBRT at a later time. SBRT will be planned as soon as the patient is recovered from surgery. Patients randomized prior to treatment will have to be treated within 4 weeks after randomization.

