### Randomization

Blocked randomization with randomly selected block sizes of 4 and 6 will be performed centrally through a web-based module (CASTOR), with stratification according to presence of extrahepatic disease and patients undergoing surgical resection. According to the intention-to-treat concept, during statistical analysis all randomized patients will be analysed in the group they were originally assigned to even when receiving a different treatment.

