### Follow-Up

Follow-up imaging and laboratory tests will be identical in both treatment arms to avoid bias with regards to both the primary and secondary endpoints such as distant progression (Fig. 2). Patients will be asked to complete quality of life questionnaires at baseline and every 3 months for the first year. All potential LTPs will be reviewed by an expert panel including independent abdominal radiologists in presence of the study PI’s.

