### Outcome Measures

The primary objective is to compare 1-year local tumour progression free survival (LTPFS) from randomisation per treated tumour in both study arms. The 1 year LTPFS is defined as the percentage of successfully eradicated tumours 12 months following treatment, according to the RECIST and PERCIST criteria with a standardised follow-up protocol. LTP successfully retreated within the first 6 months, using the same technique as the initial treatment (re-MWA or re-SBRT) will not be regarded as an event for the primary endpoint. Secondary endpoints are: OS, local control (allowing repeat treatments with the same technique) overall and distant progression-free survival (DPFS), rate of adverse events and serious adverse events, quality of life assessments using EORCT QLQ-C30, EQ-5D, and PRODISQ questionnaires prior to, and 2 weeks, 3, 6, 9 and 12 months after local treatment.

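### In patients who also have a resection, the 2-week quality-of-life form records recovery from the operation under MWA but not under SBRT

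*Protocol article*

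**What the plan says.** Outcome Measures sets the questionnaires "prior to, and 2 weeks, 3, 6, 9 and 12 months after local treatment". It does not say what counts as local treatment in a patient who has both a resection and a separate treatment of the target tumours.

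Follow-Up describes the schedule differently: "Patients will be asked to complete quality of life questionnaires at baseline and every 3 months for the first year". That sentence has no 2-week form and names no anchor for the later ones.

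Study Cohort fixes the order of events in patients with an additional lesion to be resected. They are inspected at laparoscopy or laparotomy and "if still considered eligible randomized intraoperatively". For the MWA arm: "If randomized to MWA during open laparotomy, the eligible tumours will be ablated in the same procedure using ultrasound guidance". For the other arm: "Patients included in study arm B will undergo SBRT at a later time", and "SBRT will be planned as soon as the patient is recovered from surgery". The 4-week limit from randomisation to treatment in the same section is stated for patients randomised before treatment. No limit is stated for those randomised in theatre.

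Resection is a randomisation factor (Randomization: "with stratification according to presence of extrahepatic disease and patients undergoing surgical resection"), so this subgroup is expected in both arms. The Abstract lists pain and quality of life among the main secondary endpoints.

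**The concern.** Both arms of the resection stratum undergo the operation, and both can be expected to feel worse for some weeks after it. Because the forms are counted from local treatment, the first post-treatment form falls at a different distance from the operation in each arm. Under MWA it falls in early convalescence. Under SBRT, by the protocol's own sequence, it falls after recovery. A burden common to both arms would then be recorded in one only, and the difference could be read as better tolerance of SBRT.

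Randomisation does not cancel this, because the displacement arises after allocation and depends on the arm. Analysis cannot repair it fully either: an early post-operative form that was never collected in arm B cannot be recovered. Follow-Up makes imaging and laboratory follow-up identical in the two arms in order to avoid bias, and the questionnaire anchor falls short of that aim in this stratum.

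**Working it through.** **The plan's own figure.** The article gives no figure for quality of life. Its only design calculation is for the primary endpoint ("Group sample sizes of 33 in group 1 and 33 in group 2 achieve 81.059% power"). With proportions 0.665 and 0.335 and unpooled variance, SE = √(2 × 0.665 × 0.335 / 33) = 0.1162, and power = Φ(0.33/0.1162 − 1.96) = Φ(0.880) = 0.8106. This agrees with the article, and the present point does not alter it.

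**Order of events in the resection stratum, local treatment read as treatment of the target tumours**

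| | MWA at open laparotomy | SBRT |
|---|---|---|
| Randomisation | during the operation | during the operation |
| Target treatment | same operation | later, after surgical recovery |
| 2-week form | 2 weeks after the operation | 2 weeks after SBRT, so after recovery |

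**Other reading, local treatment read as the resection.** Both 2-week forms then fall 2 weeks after the operation. The MWA form covers operation plus ablation, and the SBRT form may precede SBRT altogether. The surgical burden is now aligned, but the acute effects of SBRT may be missed.

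**Displacement on the calendar.** Assume SBRT ends 4-10 weeks after the operation (not given in the article). In weeks from randomisation the forms fall at:
- MWA: 2, 13, 26, 39, 52
- SBRT: 6-12, 17-23, 30-36, 43-49, 56-62

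**Size within the stratum.** Let d be the fall in score 2 weeks after the operation, h its recovery half-life and L the lag. All three are assumptions: d = 10-20 points on a 0-100 scale, h = 2-4 weeks, L = 4-10 weeks.

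Bias at the 2-week form = d − d × 0.5^(L/h):
- smallest (d = 10, h = 4, L = 4): 10 − 5 = 5.0 points
- largest (d = 20, h = 2, L = 10): 20 − 0.625 = 19.4 points

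Bias at the 3-month form, 11 weeks after the 2-week form = d × 0.5^(11/h) − d × 0.5^((11+L)/h):
- smallest (d = 10, h = 2, L = 4): 0.22 − 0.06 = about 0.2 points
- largest (d = 20, h = 4, L = 10): 2.97 − 0.53 = about 2.4 points

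**Size in the whole trial at 2 weeks.** Take wider assumed ranges, a resected share s of 10-50% and d of 5-20 points, with recovery complete by the SBRT form. Bias = s × d. For the chance of a false significant result at nominal two-sided 5%, assume SD 20 and 34 patients per arm, so SE = 20 × √(2/34) = 4.85.

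| s | d | Bias (points) | Chance of a false significant result |
|---|---|---|---|
| 10% | 5 | 0.5 | about 5% |
| 25% | 10 | 2.5 | about 8% |
| 50% | 20 | 10 | about 54% |

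Incomplete recovery by the SBRT form would make these figures smaller.

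**The case against.** **Timing from treatment is a legitimate choice.** It places the acute effects of each technique at the same distance from the form. When one arm is treated in one session and the other in two, no single anchor aligns both the operation and the target treatment. This stands, and it is why replacing one anchor by another is not enough. It also tells against requiring all later forms to be counted from randomisation: with a lag of 4-10 weeks, a form at week 13 would fall only 3-9 weeks after SBRT.

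**The 2-week form may not exist.** Follow-Up does not mention it. If that section governs, only the small displacement of the later forms remains. This stands as a reason to reconcile the two sections first.

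**The scope is narrow and the size is assumed.** Patients randomised before percutaneous MWA or SBRT are not affected by this mechanism. Ablation in the same procedure is explicit only for open laparotomy, although laparoscopy is also allowed. The share of resected patients is not given, and at the low end of the assumed range the whole-trial effect is negligible. All of this stands.

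**This is a condensed article.** The full protocol may define visit windows and the anchor, and the follow-up figure could not be read in the text available. That is fair for missing detail. However, the article does state an anchor and an order of events, and together these produce the imbalance.

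**Stronger readings that the article does not support.** A reader might infer that the whole quality-of-life comparison favours SBRT by construction, or that every form is seriously biased. The mechanism reaches one stratum and is already small at 3 months under the assumptions above. A reader might also infer that the interval between operation and SBRT is certainly unobserved. That depends on whether the pre-treatment form precedes the operation, which the article does not settle for these patients.

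**Conclusion.** The point holds in limited form. On the natural reading of Outcome Measures and Study Cohort, the 2-week form in resected patients records early recovery from the operation under MWA at open laparotomy but not under SBRT. The early contrast in that stratum is therefore tilted towards SBRT by timing alone. Reading local treatment as the resection removes that tilt but may place the SBRT-arm form before SBRT, so neither reading makes the arms comparable at 2 weeks.

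The size cannot be taken from the article. Under the assumed inputs the whole-trial bias at 2 weeks is about 0.5-10 points. The upper end needs half the patients to be resected and a 20-point fall. The primary endpoint and the sample size are unaffected. The correction is cheap and has to be made in data collection, so it is worth making even though the effect may prove small.

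**What to change.** 1. Reconcile Follow-Up with Outcome Measures on whether there is a 2-week form, and define the anchor for patients who have both a resection and a separate target treatment.
2. In the surgical stratum, collect a form 2 weeks after the operation in both arms, and keep the form 2 weeks after SBRT in arm B.
3. Record the date of every form. Compare the arms on actual time since randomisation, within the surgical and non-surgical strata already used for randomisation. Show both the post-operative and the post-SBRT forms, so that neither the operation nor the acute effects of SBRT are missed.
4. Whether the 3- to 12-month forms should also be counted from randomisation is a trade-off for the sponsor. Dated forms analysed on time since randomisation are enough.

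The cost is a change of wording in the schedule and one extra questionnaire for surgical patients allocated to SBRT. Treatment timing and clinical care are not affected.

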### Data Monitoring

The Clinical Research Bureau (CRB), an independent monitor committee, will safeguard the quality of this investigator-initiated study. An employee from the CRB will check the data according to Good Clinical Practice (GCP). Source Data verification will be performed during onsite monitoring (to verify if all data on the Case Report Form are in accordance with the source data). For all subjects, the informed consent forms, the inclusion and exclusion criteria and the primary outcome (1 year LTFPS) will be verified. The monitor will also verify if all (S) AE’s are reported adequately..

### Serious Adverse Events

All serious adverse events (SAE) occurring in the first 90 days after treatment, both related and unrelated will be reported within 15 days after the responsible investigator has first been notified of the SAE and within 7 days if an SAE is life-threatening or results in death. After these 90 days, only SAE’s related to the research according to one of the principal investigators, will be reported. SAEs will be reported through the web portal ToetsingOnline to the METc that approved the protocol.

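### The full SAE window starts at an undefined treatment date, so in patients who also have a resection SAE capture differs between MWA and SBRT

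*Protocol article*

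**What the plan says.** **The window.** Protocol article, Serious Adverse Events: "All serious adverse events (SAE) occurring in the first 90 days after treatment, both related and unrelated will be reported". The same section continues: "After these 90 days, only SAE’s related to the research according to one of the principal investigators, will be reported". It does not say what counts as treatment when a patient has two procedures, and it gives no rule for events between randomisation and treatment.

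**Timing in surgical patients.** Under Study Cohort, patients with an additional metastasis that needs resection are inspected in theatre and "if still considered eligible randomized intraoperatively". The arms then part:

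- MWA: "If randomized to MWA during open laparotomy, the eligible tumours will be ablated in the same procedure using ultrasound guidance".
- SBRT: "Patients included in study arm B will undergo SBRT at a later time", and "SBRT will be planned as soon as the patient is recovered from surgery".

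The one time limit in that section reads: "Patients randomized prior to treatment will have to be treated within 4 weeks after randomization". It appears to address patients randomised before any procedure, as distinct from those randomised in theatre.

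**The endpoint.** Outcome Measures lists "rate of adverse events and serious adverse events" among the secondary endpoints, and the Abstract names procedural morbidity and mortality as a main one. Under Randomization, patients are analysed in their assigned arm whatever they receive.

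**The concern.** A safety comparison between randomised arms needs a clock that starts at the same point in both. Here the operation is shared: surgical patients in either arm have a resection, and allocation is made during it. The SAE clock is tied instead to treatment, which for one arm can be the operation itself and for the other comes only once the patient has recovered from it.

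The post-operative weeks are when SAEs from the resection are to be expected. If those weeks are fully reported in one arm and not in the other, a difference in SAE rate partly reflects where the window lies rather than what MWA and SBRT do. Resection is a stratification factor, so the trial plans for such patients.

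**Working it through.** The plan gives no figure on this point, so there is none to reproduce. Sample size and power do not enter. The check is to lay the 90-day window over each arm's timeline in the surgical stratum.

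**Inputs from the article**
- Full reporting lasts 90 days after treatment; afterwards related SAEs only (Serious Adverse Events).
- Randomisation is intraoperative, so day 0 is both operation and randomisation (Study Cohort).
- MWA at open laparotomy is on day 0 (Study Cohort).
- SBRT is on day L, after recovery. L is not given.

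**Input assumed here:** L = 14, 28, 42 or 56 days, for illustration only.

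**Reading 1: treatment is the allocated MWA or SBRT.** The MWA window runs from day 0 to day 90 and covers all of the first 30 post-operative days. The SBRT window runs from day L to day L + 90 and covers max(0, 30 − L) of those 30 days.

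**Reading 2: treatment includes the resection.** Both windows run from day 0 to day 90. Full cover after the allocated treatment is then 90 days for MWA and 90 − L days for SBRT.

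| L (assumed) | Reading 1: SBRT window, days after surgery | Reading 1: first 30 post-operative days covered, SBRT (MWA: 30) | Reading 2: days of full cover after SBRT (after MWA: 90) |
|---|---|---|---|
| 14 | 14 to 104 | 30 − 14 = 16 | 90 − 14 = 76 |
| 28 | 28 to 118 | 30 − 28 = 2 | 90 − 28 = 62 |
| 42 | 42 to 132 | 0 | 90 − 42 = 48 |
| 56 | 56 to 146 | 0 | 90 − 56 = 34 |

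Under reading 1, a patient allocated SBRT who dies or deteriorates before receiving it has no day L and so no window, although the analysis keeps that patient in the SBRT arm.

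Under reading 2, the post-operative period is covered alike. The shortfall moves to the period after SBRT, where from day 90 an SAE is reported only if a principal investigator judges it related.

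If the 4-week limit were taken to apply to surgical patients too, L could not exceed 28 days. At that limit, reading 1 still covers only 2 of the first 30 days for SBRT.

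In patients treated without surgery, the 4-week limit bounds the uncovered interval in both arms. The problem is therefore confined to the surgical stratum.

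**The case against.** The strongest reply is that this section governs reporting to the ethics committee, with its deadlines and web portal, and does not define the endpoint. Outcome Measures attaches no 90-day window to the SAE rate. Data Monitoring describes case report forms checked against source, so an SAE outside the reporting window may still be recorded and analysed. The section also restricts reporting only after the 90 days; it does not say that earlier events are to be ignored. This stands as a limit on certainty: biased counting is possible but not demonstrated. It does not remove the point, because no other SAE window is stated and the stated one has an unclear start.

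A second reply is that treatment naturally includes the resection. That is tenable and closes the post-operative gap, but it uses up part of the 90 days before SBRT begins.

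Some stronger readings are tempting but not supported:

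- *Surgical morbidity counts against MWA only.* Even under reading 1, post-operative events after SBRT starts are covered (16 of 30 days at an assumed 14-day interval).
- *All surgical MWA patients are ablated during the operation.* The article says so only for open laparotomy; the laparoscopic route is not spelled out.
- *SAEs after retreatment within 6 months escape reporting.* The section says treatment, not first treatment, and related SAEs remain reportable in both arms without a time limit.
- *Deaths before SBRT are lost to the trial.* Overall survival is a secondary endpoint and would capture them.

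**Conclusion.** The concern holds in this limited form. The start of full SAE reporting is badly fixed for patients who have both resection and SBRT. On either reading of treatment, SAE capture differs by arm in the surgical stratum: around the operation on the first, after SBRT on the second. This can bias the secondary comparison of SAE rates. Both readings give the SBRT arm less cover, so the likelier direction is too low an SAE count for SBRT relative to MWA. The primary endpoint, sample size and power are untouched.

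The size cannot be stated. The article gives neither the share of surgical patients nor the surgery-to-SBRT interval, and the days in the table rest on assumed intervals. A reader might build a figure by supposing 7 to 10 surgical patients among the 34 allocated SBRT and a 10–20% risk of an SAE before SBRT: 7 × 0.10 = 0.7 to 10 × 0.20 = 2.0 events, or 0.7/34 = 2.1% to 2.0/34 = 5.9%. Neither input has any anchor in the article, so this should not be quoted as the size of the bias.

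**What to change.** Amend Serious Adverse Events so that all SAEs, related or not, are reported and recorded from randomisation in both arms until 90 days after the last allocated study treatment. Say when collection ends for a patient who never receives the allocated treatment. State that SAE rates are compared by assigned arm from randomisation.

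One detail needs care. Collection will then last 90 days in a surgical MWA patient treated once on day 0 and L + 90 days in a surgical SBRT patient treated once. The comparison should therefore use the same number of days from randomisation in both arms, with MWA collection extended to that day if needed.

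The cost is a short amendment and a few more SAE reports. Treatment timing, sample size and the primary analysis do not change.

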## Discussion

Currently, guidelines state that thermal ablation can be applied for unresectable CRLM of limited-size (≤ 3 cm) and that SBRT should be considered if the location of the tumour is unfavourable for thermal ablation [19–21]. However, the preferred treatment option for intermediate-size unresectable CRLM (3-5 cm) has not been established. Following both thermal ablation and SBRT, LTP rates increase with larger tumour size [17, 22–28]. Patients eligible for both treatment options often receive extensive chemotherapy in an attempt to downstage patients from unresectable disease to resectable disease [20]. If tumours remain unresectable, thermal ablation and SBRT are a ‘last resort’ local curative intent treatment option with a presumed superior oncological outcome [3, 20].

The current primary efficacy rate of thermal ablation (complete ablation after the first procedure) for CRLM ≤ 3 cm (92–100%) is approaching to local recurrence rates after surgery for similar sized tumours [11, 29–32]. However, multiple studies have shown that efficacy significantly decreases to below 80% following thermal ablation of CRLM > 3 cm [11, 24, 33, 34]. For these larger-size tumours, novel MWA generation systems or tumour-bracketing multiprobe ablation techniques are preferred.As wide peri-ablational margins with > 5 mm margins, and if possible > 10 mm, are associated with technical success (A0 ablations), multiple electrodes may be used to increase the size of the ablation zone [35]. With the use of MWA, higher intra-tumoural temperatures, faster heating, shorter procedure times and larger ablation volumes with wider margins can be achieved, even in larger tumours [36–38]. Also, due to its active heating mechanism MWA might be less susceptible to the “heat-sink” effect of conductive heating with RFA [37].

The 1- and 2-year local control rate for SBRT in multiple studies (all retrospective or prospective cohort studies) ranges from 50 to 95% and 45–92%, respectively [39–49]. Several studies showed that increased tumour size had a negative influence on the local control rate [43, 44, 50]. Even with increased tumour sizes, SBRT can be administered safely when a tumour is located in proximity to the gallbladder, bile ducts, main vessels and the diaphragm. No anaesthesia is required and recent advances in SBRT techniques seem to have reduced radiation induced toxicity. With this new magnetic resonance (MR)-guidance technique, the tumour is visualized during radiation delivery. Radiation can be delivered “gated” (i.e. beam-on only when the tumour is in the predetermined position) using small uncertainty margins and thereby limiting the dose delivered to normal organs, likely resulting in decreased toxicity [51, 52]. Nonetheless, major complications still occur in 0–9% and toxicity grade I-II occurs in 23–78% of patients [43, 50, 53–56].

Studies directly comparing thermal ablation to SBRT for intermediate-size CRLM are scarce. One recent study compared thermal ablation to SBRT for all sizes of unresectable CRLM, where results should be interpreted with caution, because of potential residual confounding due to non-randomized nature and selection bias [57]. The LTPFS and LC significantly improved in the thermal ablation group compared to the SBRT group for all sizes. In addition, stratification of results of intermediate size CRLM significantly favoured thermal ablation over SBRT. In this study, size of CRLM was a significant predictor for development of LTP in the thermal ablation group. Nonetheless, size of CRLM did not predict the development of LTP in the SBRT group. Therefore, it was suggested that SBRT might be less susceptible to larger tumour-sizes. In contrast, a recent propensity score-based comparison of LC favoured SBRT over thermal ablation for intermediate size CRLM [16]. We chose to allow for one re-ablation for local tumour progression if detected within 6 months. It would otherwise be unjust to compare an easily repeatable ablative method (MWA) to a treatment that is more difficult to repeat safely (SBRT).

To conclude, as current guidelines lack clear recommendations for treatment of intermediate-size CRLM and as studies comparing the potential treatment options, SBRT and thermal ablation, are scarce, studies directly comparing the two treatment options are indispensable. COLLISION-XL represents a two-arm phase-II/ III randomized controlled trial directly comparing SBRT to MWA for unresectable, intermediate size CRLM.

